Sample size: We will recruit 120 participants from the eight randomised clusters. Formal power calculations are not necessary as no hypothesis testing for trial effectiveness is being evaluated.^55^ A sample of 120 (with ~60 per arm) meets sample size recommendations for pilot and feasibility studies and is sufficient to provide precision of feasibility parameters and estimates of study summary measures for a definitive trial.^56^ 20 participants in total will be recruited for focus groups (three groups of five diverse participants) and five 1:1 interviews.

Analysis: Descriptive statistics will be used to assess training fidelity and feasibility outcomes. Other data will be analysed using thematic analysis to generate important themes and patterns.^57 58^ For the secondary outcomes, means, CIs, intra-cluster correlation coefficient (ICC) of the outcome measures (both within-study and between-study clusters) will be estimated to determine which outcome(s) are most sensitive to change and provide sample size calculation for definitive trial.

ICCs for each quantitative outcome will be estimated using mixed-effects regression models including a random intercept for clusters, following the approach recommended by Hemming *et al* for cluster and stepped-wedge feasibility studies.^59^ Analyses will be undertaken in Stata (V.18). The ICC estimates, along with observed variances and completion rates, will inform the design of the definitive trial by (i) identifying outcomes that are most sensitive to change and (ii) providing parameter estimates for sample size and power calculations.

Missing data will be assessed for extent and pattern. The proportion of missing values for each variable will be reported, and exploratory analyses will assess whether missingness appears random or systematic. As this is a feasibility study, no formal imputation will be undertaken for primary feasibility outcomes; however, simple sensitivity analyses using mean or regression-based imputation may be conducted to evaluate the potential impact of missing data on secondary outcomes.^55 56^ The findings will inform strategies for minimising and handling missing data in the future definitive trial.

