#### WP2: a pilot SWCRT of e-learning for mental health professionals

Research question: Is an e-learning module on culturally responsive care feasible and acceptable for delivery to NHS mental health professionals?

Design: Pilot stepped-wedge cluster randomised trial assessing feasibility, uptake and change in multicultural competence scores.

Aims and objectives: To evaluate the feasibility and acceptability of the e-learning to inform our implementation evaluation in a future trial (phase 3).

Design: We will adopt a pragmatic SWCRT^60^ design with random and sequential crossover of clusters (youth mental health teams) from control to intervention (our e-learning module) until all clusters are exposed. Because training is delivered openly within existing clinical teams, outcome assessment cannot be blinded; feasibility endpoints are objective and carry minimal risk of bias.

Methods: There will be a phased and sequential implementation of the e-learning at regular intervals across teams and trusts over a 6-month period (months 4–9; figure 3). Staff will complete the training outcome measure before and after the e-learning.

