**Figure 3 F3:**
[figure not shown]
Co-STARS e-learning stepped-wedge rollout. This schematic shows the sequential rollout of the e-learning intervention across six clusters over the 12-month study period. *Forward Thinking Birmingham of Birmingham Women’s and Children’s NHS Foundation Trust (FTB of BWC NHS FT). **Early Intervention Services of Black Country Healthcare Foundation Trust (EIS of BCH NHS FT).

The training will be deployed in a staggered manner in line with the stepped wedge approach. Starting in the first Mental Health Trust (Forward Thinking Birmingham (FTB) of Birmingham Women’s and Children’s NHS Foundation Trust; please see setting for description) in month 4 and rolled out to the four teams in staggered intervals. The training will then be rolled out in the second Mental Health trust (Early Intervention Services (EIS) of Black Country Healthcare NHS Foundation Trust) with staggered implementation between months 6–9. Through the course of implementation, we will conduct staff focus groups and semi-structured interviews. Baseline (pre-training) and post-training (4 weeks later) data will be collected electronically via the NHS Learning Hub platform.

Setting: FTB, part of the Birmingham Women’s and Children’s NHS Foundation Trust, is a 0–25 years community and inpatient mental health service and is the primary mental health service regionally for this population. Within FTB, there are four specialised care pathways, including Youth Justice, Specialist Eating Disorders and Core mental health team and EIS, which offer intensive community support to young people with a FEP.

The second trust is Black Country Healthcare NHS Foundation Trust, in which we will target four EIS teams (Dudley, Walsall, Sandwell and Wolverhampton), which provides community support to young people with psychosis between the ages of 14 and 65 years.

Randomisation: Cross-over of clusters (clinical team; n=6) from control to intervention will occur approximately every 4 weeks.

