Population: *Inclusion criteria*: NHS staff working within participating teams. *Exclusion criteria:* administrative personnel not directly engaged in mental healthcare delivery. Recruitment will occur via internal staff communications and service managers. A range of professionals (n=120) will be expected to complete the training, including psychiatrists, psychologists, community psychiatric nurses, occupational therapists, support workers and social workers. A purposive sampling method will be used to recruit staff to the focus groups and 1:1 interview, ensuring a balance of staff backgrounds, experience and representation from across different teams and trusts. We will also adhere to INCLUDE guidelines to ensure diversity and inclusion in our sampling.^61^

Intervention: The intervention is a 60 min e-learning module targeted at professional systems and public organisations involved in mental healthcare pathways. This e-learning is hosted by the NHS Learning Hub platform. Informed by lived experience, the e-learning seeks to raise awareness of sociocultural diversities, awareness of cultural barriers, multicultural knowledge and sensitivity and responsiveness to patients from Black ethno-racial backgrounds.

Control: The control condition will be the unexposed observation period before sequentially crossing over to the exposed observation period (receiving the intervention).

Outcome: Feasibility process outcomes will include training uptake, defined as the proportion of eligible staff completing the e-learning module within each cluster, and acceptability, assessed quantitatively through completion and satisfaction rates and qualitatively via staff focus groups and interviews exploring the training’s perceived relevance, usefulness and delivery.^62^ The qualitative component will be guided by the Acceptability of Intervention Measure framework. Secondary outcome will be assessed using the California Brief Multicultural Competence Scale (CBMCS),^63 64^ which assesses mental health staff knowledge, attitudes, skills and competencies when working with minoritised groups. The CBMCS has shown strong reliability (Cronbach’s α=0.91) and construct validity across diverse healthcare professional samples.^63 64^ Pre-training and post-training CBMCS scores will be compared at individual and cluster levels to estimate mean change and ICCs.

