Sample size: Formal power calculations are not necessary as no hypothesis testing for trial effectiveness is being evaluated.^55^ A sample of 120 meets sample size recommendations for pilot and feasibility studies and is sufficient to provide precision of feasibility parameters and estimates of study summary measures for a definitive trial.^56^

Analysis: Descriptive statistics will summarise training uptake, completion rates and acceptability indicators for each cluster and step period. Quantitative comparisons of pre-training and post-training CBMCS scores will be undertaken using mixed-effects linear regression models with a random intercept for cluster and a fixed effect for time step, following Hemming *et al*’s recommendations for stepped-wedge feasibility trials. Analyses will be performed using Stata (V.18).

Qualitative acceptability data will be analysed thematically to identify perceived enablers and barriers to implementation.

Estimates of outcome variability, ICCs and temporal trends will be reported with 95% CIs to inform sample size and power calculations for the definitive trial.

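### The WP2 mixed model has no staff-level term for paired CBMCS scores, so the intervals for the pre/post contrast would be about 1.2 to 1.6 times too wide

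*Protocol article*

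**What the plan says.** The WP2 Methods paragraph sets up paired data: "Staff will complete the training outcome measure before and after the e-learning". The rollout text under Figure 3 fixes the interval: "Baseline (pre-training) and post-training (4 weeks later) data will be collected electronically via the NHS Learning Hub platform". Under Randomisation, "Cross-over of clusters (clinical team; n=6) from control to intervention will occur approximately every 4 weeks", and under Population, "A range of professionals (n=120) will be expected to complete the training".

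The Outcome paragraph states the aim: "Pre-training and post-training CBMCS scores will be compared at individual and cluster levels to estimate mean change and ICCs". The Analysis paragraph gives the model as "mixed-effects linear regression models with a random intercept for cluster and a fixed effect for time step". It opens that sentence with "Quantitative comparisons of pre-training and post-training CBMCS scores will be undertaken using", so the model is meant to carry the pre/post comparison. The same paragraph says that outcome variability, ICCs and temporal trends will be reported with 95% CIs to support sample size and power calculations for the definitive trial.

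**The concern.** Two scores from one person 4 weeks apart will be correlated well beyond what shared team membership explains. A model with a team intercept as its only random effect puts the stable differences between people into the residual. The pre/post contrast is largely a within-person comparison, in which those differences cancel, but the model charges them to its standard error all the same.

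At stake are the error bars on the training contrast and on the time steps, a small upward push on the team ICC, and the loss of one planning quantity. A later design with repeated scores on the same staff would need the within-person correlation, and this model cannot supply it.

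**Working it through.** **Inputs from the protocol.** 6 teams, 120 staff, crossover about every 4 weeks, second score 4 weeks after the first. This gives 120/6 = 20 staff per team on average and 2 × 120 = 240 scores if all pairs are complete. The 120 rests on pilot-study recommendations, and no SD, ICC, effect size or standard error is stated, so there is no figure of the plan to reproduce.

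**Assumptions.** Equal teams (m = 20); complete pairs; team k scored before training in period k and after it in period k+1; total variance 1, so results are in SD units; team ICC 0.02 to 0.10; within-person correlation ρ 0.5 to 0.8. The variance components are team v_c = ICC, staff v_i = ρ − ICC, and residual v_e = 1 − ρ. A pre/post indicator is granted to the planned model throughout.

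**Step 1: without time steps (can be checked by hand).** The cluster-only model reports SE = √[2(1 − ICC)/120]. The true SE of the paired mean difference is √[2(1 − ρ)/120]. With ICC 0.05 and ρ 0.6:
- reported: √(2 × 0.95/120) = 0.126
- true: √(2 × 0.40/120) = 0.082
- ratio: √(0.95/0.40) = 1.54

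**Step 2: with the time steps that the plan includes.** Let X hold the intercept, six step indicators and the pre/post indicator. Let V_w be the working covariance (team + residual only) and V the true covariance (team + staff + residual). The estimator is b = By with B = (X′V_w⁻¹X)⁻¹X′V_w⁻¹. The model reports the variance (X′V_w⁻¹X)⁻¹, whereas the true variance is BVB′. With the team variance in V_w held at its true value, the SEs of the pre/post contrast are as follows (ratios from unrounded values):

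| ICC | ρ | Reported SE | True SE | Ratio |
|---|---|---|---|---|
| 0.02 | 0.5 | 0.145 | 0.114 | 1.27 |
| 0.02 | 0.8 | 0.145 | 0.090 | 1.62 |
| 0.05 | 0.5 | 0.150 | 0.121 | 1.24 |
| 0.05 | 0.6 | 0.150 | 0.114 | 1.31 |
| 0.05 | 0.7 | 0.150 | 0.106 | 1.41 |
| 0.10 | 0.5 | 0.156 | 0.132 | 1.18 |
| 0.10 | 0.8 | 0.156 | 0.110 | 1.42 |

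Over the grid the ratio runs from 1.18 to 1.62. If V_w instead carries the inflated team variance of Step 4, it runs from 1.20 to 1.69. The estimate itself loses almost nothing: at ICC 0.05 and ρ 0.6 its true SE is 0.114, against 0.113 with a staff intercept. A 60-run REML simulation at those values agrees. The cluster-only model reported a mean SE of 0.151 against an empirical SD of 0.109; with a staff intercept the figures were 0.115 and 0.108.

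**Step 3: time-step effects.** At ICC 0.05 and ρ 0.6, with the inflated team variance, the reported SEs run from 0.307 (first step) to 0.517 (last), against true values of 0.217 to 0.474. The ratios are 0.307/0.217 = 1.41 and 0.517/0.474 = 1.09.

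**Step 4: team ICC.** A team mean over 2m scores has variance v_c + v_i/m + v_e/(2m). The cluster-only model expects v_c + (v_i + v_e)/(2m), so its team variance absorbs the difference, v_i/(2m). At ICC 0.05 and ρ 0.6 this is 0.55/40 = 0.014, which moves the ICC from 0.05 to 0.06375/1.01375 = 0.063. Over the grid, 0.02 becomes 0.032 to 0.039, 0.05 becomes 0.061 to 0.067, and 0.10 becomes 0.109 to 0.115. In the 60-run REML simulation the two mean ICCs were practically equal (0.0614 and 0.0613), so 0.01 to 0.02 is best read as an upper figure.

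**The case against.** **The pairing may be handled through change scores.** The Outcome paragraph speaks of mean change at individual level, and a model of change needs no staff intercept. But the Analysis paragraph applies its model to the pre-training and post-training scores, with an effect for time step. With one change per person and one crossover per team, step would coincide with team and could not sit beside a team intercept. The change-score reading does not fit the model as written.

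**An article condenses, and an analysis plan may list more terms.** This is fair in general. Here, though, the protocol itself names the random-effects structure, and nothing elsewhere in it points to a staff-level term.

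**The error is conservative and the outcome secondary.** This stands. Intervals that are too wide lead to no false claim of benefit, no effectiveness hypothesis is tested, and feasibility outcomes decide progression. The SE of the training contrast is also not among the quantities listed for Phase 3.

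**The ICC shift is minor.** This stands too. With six teams, even the correctly specified ICC estimate has a central 95% sampling range of about 0 to 0.17 when the true value is 0.05. A shift of 0.01 to 0.02 is small beside that.

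**Stronger readings that the text does not support.** A reader might infer that the model has no exposure term and that the temporal trends will therefore be biased. But the sentence introduces the model as the means of the pre/post comparison, so the contrast is implied. Bias would follow only if the term were really left out: in that case a 0.5 SD training effect with no secular trend would give step coefficients of 0.33 to 0.96 SD. That is a reason to write the term out, not evidence that it is missing. A reader might also infer that the WP1 ICC model lacks an arm or baseline term. Its wording, "ICCs for each quantitative outcome will be estimated using mixed-effects regression models including a random intercept for clusters", lists what the model includes and does not exclude other terms.

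**Conclusion.** The point holds for the missing staff-level term. As written, the WP2 model overstates the SE of the pre/post contrast by about 1.2 to 1.6 times and misstates the SEs of the time steps. It raises the team ICC slightly and leaves the within-person correlation unestimated. The sizes depend on assumed variances, equal teams of 20 and complete pairs. The direction needs only that scores within a person correlate more strongly than scores of different people in the same team.

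The documents do not establish that the exposure term is absent, that the time trends are biased, or that the WP1 ICC model is wrong. Calling the WP2 ICC itself wrong would also go too far. Severity is moderate.

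**What to change.** State the WP2 model as CBMCS on time step and a pre/post exposure indicator, with random intercepts for team and for staff within team, fitted by REML with a small-sample degrees-of-freedom correction. In Stata: `mixed cbmcs i.step i.exposed || team: || staff:, reml dfmethod(kroger)`. Writing the exposure indicator out makes clear that the reported temporal trends are separated from the training effect. Report the team ICC and the within-person correlation, each with its 95% CI.

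The cost is a sentence of text and one line of code, with no new data. The two scores must be linked by person, which the planned individual-level comparison already requires.

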#### WP3: mixed-methods study: systems mapping and systems change

Research question: What system-level mechanisms link the Co-STARS intervention to improved access and outcomes for Black young people?

Design: Realist-informed mixed-methods study combining participatory systems mapping, Delphi consensus and exploratory time-series analysis.

We will conduct a mixed-method, realist-informed process evaluation to support a proposed whole-systems approach for assessing the impacts of the training model described in WP 1 and 2. This process evaluation will explore *how*, *why*, *for whom* and *under what circumstances* the training may generate whole systems change (online supplemental material 1). We will further explore system-level mechanisms.

Systems map: A systems map^65^ will be developed in three phases: (1) First, we will undertake a concept mapping workshop involving key stakeholders (patients, research team, providers and policymakers). This will be guided by a draft model produced by the team (who consist of mental health experts in the region) which will then be introduced and amended using an iterative consensus building process in a face-to-face workshop. (2) This will be followed by a modified two-stage modified Delphi survey inviting regional mental health experts to provide their agreement or disagreement with the systems map and willingness to be involved in semi-structured interviews with the research team. (3) Those willing to take part in interviews will then be invited to share their opinions on how the intervention may impact the system map and in particular their opinion on potential outcomes which should be measured at a system-wide level.

Exploring the early impacts of co-STARS: To identify whether the intervention is providing tangible impacts on a system-wide level, we are proposing to pilot a data-driven impact evaluation. We are planning to undertake an interrupted time series (ITS) to ascertain whether the introduction of the intervention leads to a change in the relevant outcomes identified in the systems mapping process. This type of analytical approach has been advocated for use in public health evaluations and is related to structural break modelling.^66^

This pilot evaluation will be undertaken in three phases: (1) Identification of suitable data sources: Guided by health data science expertise in the research team, expert opinion from the systems mapping process and through open source searching, we aim to compile a directory of suitable datasets and outcomes which could inform the systems wide impact of the intervention. For example, West Midlands Police Data will be used to examine the rate of detentions under Section 136 of the UK Mental Health Act among Black males. These detentions represent police-initiated transfers of individuals appearing mentally unwell from public settings to a place of safety for clinical assessment. Data sources will include open-access administrative datasets (eg, NHS Digital, West Midlands Police s136 statistics) and local health service indicators, each evaluated for completeness and temporal resolution before inclusion. (2) Trial of ITS model: Using available datasets (those open access or those already accessible by the research team), we will undertake a pilot ITS. The study period will be set between 2022 and 2024. Incidence rates (calculated by the number of new cases divided by the at-risk population) will be analysed on a monthly basis (weekly where possible) throughout the study period and these trends will be depicted graphically. The primary break point that will be examined is the introduction of the intervention; thus, monthly data 1 year prior and 1 year following this timepoint will be included. We will examine the sensitivity of the analysis around this break point. (3) Stakeholder engagement: We plan to undertake three focus groups (consisting of six to eight people) with key stakeholders (patients, providers and commissioners) to demonstrate our findings from the trial to unpick the possible mechanisms for these changes as a result of the impact of the intervention of the systems map. The secondary aim of these focus groups will be to optimise the strategy to undertake such systems change evaluation of a broader scale when the intervention is rolled out for a full trial.

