**Methods and analysis:**

We co-produced a culturally appropriate, place-based, tiered MHL training package (Co-STARS) to deliver within underserved Black communities and via an e-learning package implemented among staff within mental health trusts. The training will be evaluated in stages. First, a pilot cluster randomised controlled trial will assess the feasibility and acceptability (defined as participants’ perceptions of the training’s relevance, usefulness and delivery) of a lived experience-led MHL training package delivered by Black young people with experience of mental ill health, to underserved communities in Birmingham, UK. Acceptability will be quantified through participation and completion rates and explored qualitatively via focus groups and interviews. Second, a stepped-wedge cluster randomised trial will evaluate the feasibility of an e-learning training programme for mental health professionals. We will embed a process evaluation to explore change mechanisms and identify barriers and enablers for future implementation. Third, we will use realist-informed participatory systems mapping and novel epidemiological analyses to explore downstream effects (ie, improved care access for Black ethno-racial groups within the intervention areas). Last, a cost-effectiveness framework will be developed to assess whether the intervention is good value for money in future efficacy trials. In the cluster trial, eight clusters will be randomised to the intervention arm (face-to-face training in the community) and control arm (display of MHL materials) with pre- and post-assessments in 120 participants from 8 clusters, 3 weeks apart. In the stepped wedge trial, six clusters (clinical teams within NHS mental health trusts) including 120 NHS staff in total, will move from control phase to intervention phase in a stepped wedge manner, with pre-assessments and post-assessments.

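### WP3 gives its pilot interrupted time series a causal aim, but the stated design is a single before/after series with no comparison and a window that ends before the intervention starts, so no change could be attributed to the intervention

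*Protocol article*

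**What the plan says.** The Abstract (Methods and analysis) says the epidemiological work will explore downstream effects, glossed as "improved care access for Black ethno-racial groups within the intervention areas". The WP3 design line describes a "Realist-informed mixed-methods study combining participatory systems mapping, Delphi consensus and exploratory time-series analysis".

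Under *Exploring the early impacts of co-STARS*, the aim is stated twice: "To identify whether the intervention is providing tangible impacts on a system-wide level, we are proposing to pilot a data-driven impact evaluation", and the ITS is "to ascertain whether the introduction of the intervention leads to a change in the relevant outcomes identified in the systems mapping process".

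The three phases of the pilot evaluation then fix the following:

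- **Data.** Sources are still to be compiled. One example is given: "West Midlands Police Data will be used to examine the rate of detentions under Section 136 of the UK Mental Health Act among Black males". NHS Digital data and local health service indicators are also listed.
- **Model.** The study period is 2022 to 2024. Rates are monthly, or weekly where possible. The primary break point is the introduction of the intervention, with one year of data on each side and a sensitivity check around the break. No comparison series is mentioned.
- **Use.** Stakeholder focus groups are shown the findings "to unpick the possible mechanisms for these changes as a result of the impact of the intervention of the systems map". A secondary aim is to improve the strategy for the full trial.

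On exposure, WP1 states: "We will recruit 120 participants from the eight randomised clusters", with about 60 per arm and 1:1 allocation. WP2 expects 120 NHS staff to complete the e-learning. The opening of the main Methods section says that recruitment started in March 2025 and that effectiveness is not tested in this phase.

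**The concern.** The aim and the planned use of the result both presume attribution, and the design cannot supply it. In a single series with one break, the counterfactual is only the extrapolated pre-period. Anything else that changed at about the same time, such as policing practice, service reorganisation or recording, falls into the same coefficient. Moving the break point tests timing; it does not remove a concurrent cause.

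Two misreadings could follow. A break caused by something else could be handed to stakeholders to find mechanisms for, and those mechanisms could shape the Phase 3 theory of change. Conversely, a flat series could be read as a sign that the community training does not work, when the exposure was too small for the series to show it. The stated calendar window adds a separate problem: it appears to contain no post-intervention data.

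**Working it through.** **1. Exposure through WP1.** Inputs: 120 participants, eight clusters, 1:1 allocation (WP1, Sample size and Unit of randomisation); 5000–15 000 residents per MSOA (Unit of randomisation); Black population share 19% in West Birmingham and 9% in Birmingham (WP1, Setting).

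- The protocol's own figure reproduces: 120/2 = 60 per arm. Intervention areas: 8/2 = 4 MSOAs.
- Residents: 4 × 5000 = 20 000 to 4 × 15 000 = 60 000.
- Share trained: 60/60 000 = 0.1% to 60/20 000 = 0.3%.
- Share of Black residents, if every trainee is Black: at 19%, 60/11 400 = 0.5% to 60/3800 = 1.6%; at 9%, 60/5400 = 1.1% to 60/1800 = 3.3%.

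If trainees have average baseline risk and there is no spread to others, removing their risk entirely lowers the area rate by no more than these shares. Halving it lowers the rate among Black residents by about 0.3–1.7%. WP1 eligibility requires neither Black ethnicity nor male sex, so for an outcome in Black males these values are generous.

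**2. What 24 monthly points can detect.** The documents give no event counts, so I assume m = 20–50 events a month, Poisson variation, two-sided 5% and 80% power (1.96 + 0.84 = 2.80).

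- Without a trend term: SE(log rate ratio) = √(2/(12m)), which is 0.091 at m = 20 and 0.058 at m = 50. Detectable fall = 1 − exp(−2.80 × SE) = 22.6% and 14.9%.
- With a linear trend, which an ITS needs, the squared correlation between time and the step over 12 + 12 points is 0.75 × 576/575 = 0.751. The SE is therefore multiplied by 1/√(1 − 0.751) ≈ 2.0, giving about 0.183 and 0.116. Detectable fall: about 40% and 28%.
- Over a wider assumed range, 10 to 200 events a month, the trend-adjusted values run from about 52% to 15%. With a variance twice Poisson, the values at 20 and 50 a month rise to about 52% and 37%.

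So a direct WP1 effect of at most about 3% among Black residents is set against a detectable fall of 28–40%. A series covering more than the four MSOAs would dilute the effect further.

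**3. Exposure through WP2.** Staff act through their patients. Adding the headcounts (60 + 120 = 180, or 0.3–0.9% of 20 000–60 000) does not bound that effect, so the comparison above is confined to WP1.

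**4. Calendar.** Recruitment began in March 2025. If that month is the earliest possible break, 12 + 12 months runs from March 2024 to February 2026. The overlap with 2022–2024 is March to December 2024: 10 months, all before the break. Months after March 2025 inside the stated window: 0. Both work packages also phase delivery over project months 4–9, so a single break date only approximates the introduction.

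**The case against.** The strongest reply is that the protocol already presents this as a pilot. The time series is labelled exploratory, sources are checked for completeness and temporal resolution, the break point is varied, the focus groups discuss possible mechanisms and also help to improve the Phase 3 strategy, and effectiveness testing is disclaimed. The article condenses a fuller protocol, and the choice of a control series could sit there. This reply softens the point. It does not remove it, because the article itself states the causal aim, the break point, the window and the attributing use of the results.

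Four stronger readings are tempting but unsupported.

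- A reader might infer that only about 60 people are exposed, so a null is expected however good the training is. WP3 assesses the training of WP1 and WP2 together, and staff training could reach many patients. The argument from small exposure holds for WP1 only.
- A reader might infer that the data are police-force-wide. The article does not state the geographic level of the police series and gives it as one example among other sources, some of them local. What can be said is that no series is restricted to the intervention areas.
- A reader might infer that any change seen must have another cause. The design shows only that a change could not be attributed.
- A reader might quote the 15–23% detectable fall from step 2. It comes from an untrended comparison and assumed counts, and it understates what an ITS would need.

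**Conclusion.** The point holds as a mismatch between aim and design. With one series, one break and no comparison, the WP3 ITS cannot say whether the intervention leads to a change, for either training route. For WP1, the direct effect on area rates is probably far below what the series can detect. That rests on assumed monthly counts, average baseline risk among trainees, little spread beyond them, and population shares from West Birmingham and Birmingham as a whole; the sampled MSOAs are described only as intermediate in Black population density. The size of the WP2 effect is open. The date conflict needs no such assumption beyond the intervention not preceding recruitment: the stated window holds no post-intervention month and must be reconciled with the planned year of follow-up. None of this affects the WP1 or WP2 feasibility outcomes.

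**What to change.** - Restate the WP3 ITS as a test of data availability and model feasibility (completeness, monthly counts, pre-period trend, autocorrelation and overdispersion), with no claim that the intervention changed rates. This agrees with the protocol's own statement that effectiveness is not tested in this phase.
- Reconcile the 2022–2024 window with the rollout dates and with the year of data planned after the break. If a historical model run is intended, say so and drop the post-intervention wording.
- Add a comparison series from the same dataset, for example non-Black males, or the WP1 control MSOAs where small-area data exist.
- Reword the focus-group task to how such a series should be designed and read in Phase 3.

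The cost is protocol wording and one further series, with no new participants; the sponsor gives up an impact statement that the pilot cannot support. The comparison is imperfect. WP2 training may reach control areas and non-Black patients, WP1 is open to non-Black residents, and MSOA counts may be sparse: at a 19% share, and assuming half are male, four MSOAs hold about 1900–5700 Black males of all ages. The comparison should therefore be reported as descriptive only.
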